## Abstract

**Background:**

Falls are a common problem among older adults that lead to injury, emergency department (ED) visits, and institutionalization. The Apple Watch can detect falls and alert caregivers and clinicians that help is needed; the device could also be used to objectively collect data on gait, fitness, and falls as part of clinical trials. However, little is known about the ease of use of this technology among older adult ED patients, a population at high risk of recurrent falls.

**Objective:**

The goal of this study—the Geriatric Acute and Post-Acute Fall Prevention Intervention (GAPcare) II—is to examine the feasibility, acceptability, and usability of the Apple Watch Series 4 paired with the iPhone and our research app Rhode Island FitTest (RIFitTest) among older adult ED patients seeking care for falls.

**Methods:**

We will conduct field-testing with older adult ED patients (n=25) who sustained a fall and their caregivers (n=5) to determine whether they can use the Apple Watch, iPhone, and app either (1) continuously or (2) periodically, with or without telephone assistance from the research staff, to assess gait, fitness, and/or falls over time. During the initial encounter, participants will receive training in the Apple Watch, iPhone, and our research app. They will receive an illustrated training manual and a number to call if they have questions about the research protocol or device usage. Participants will complete surveys and cognitive and motor assessments on the app during the study period. At the conclusion of the study, we will solicit participant feedback through semistructured interviews. Qualitative data will be summarized using framework matrix analyses. Sensor and survey response data will be analyzed using descriptive statistics.

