#### ED Procedures

The following steps will be taken for device setup *prior* to patient approach:

Charge and pair the Apple Watch and iPhone via Bluetooth; for participants with their own devices, pairing will occur in real time.Maximize font and icon size on both devices to enhance readability.Set brightness at its maximum to improve readability.Delete irrelevant content and minimize notifications (eg, remove and mute unnecessary apps and notifications, respectively) to limit distractions.Download the RIFitTest app from the Apple App Store onto the iPhone.Add the study principal investigator and an emergency contact to the contact list to receive fall alert notifications.

Training in the use of the iPhone, Apple Watch, and RIFitTest app as well as study-related activities will also be provided, including the following:

iPhone and Apple Watch setup instructions, including how to turn the device on and off, unlock and set a password, and charge both devices.Real-time demonstration of *active tasks* accessed through the study app.A demonstration of how to log a fall and/or injury through the app.Education in the research protocol, including when to use the Apple Watch (ie, continuously, including while bathing and participating in water activities), nightly charging of iPhone, mealtime charging of the Apple Watch, daily completion of fall surveys, and weekly completion of *active tasks* on the RIFitTest app.Orientation to the study materials: file, business card with hotline for assistance, technology manual (see Multimedia Appendix 1), calendar of assessment timing, technology agreement, and consent form.

Figure 1 illustrates a timeline of the study that will be explained to participants.

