#### Follow-up Procedures

Study participation will last for 30 days or until the participant is no longer able or willing to participate. All participants will be contacted by research staff on days 3, 8, 15, and 22 to remind them to complete the steps in the study protocol and to answer questions. Participants will take part in a 30-minute semistructured interview at the completion of the study period. The interview will be conducted by the principal investigator and her staff. The intent of the interview will be to record participants’ experience with the study as well as to provide information on the feasibility, usability, and acceptability of the Apple Watch, iPhone, and RIFitTest app. Participant feedback about the quality of the intervention materials will also be solicited. The information collected in the interview will be used to improve the app and training procedures in preparation of the subsequent clinical trial.

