	**Apple Watch sensor-obtained measures**			
		Apple Watch measures (ie, accelerometer, gyroscope, and physiological sensors)	Gait and fitness (ie, time spent walking, standing, and climbing steps; 4-meter walk gait speed test; and resting heart rate) Data will include cognitive and active task performance, including cadence and walking speed related to their gait and balance and Stroop test. Performance reports will be generated for each participant.	Baseline ± continuously (days 1 to 30)

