### Sensor and Survey Data Collection and Analysis

Continuous data collected by the Apple Watch will be sourced from the accelerometer, gyroscope, heart rate monitor, and GPS sensors. Episodic data that will be collected include electronic health record data, fall dairy, Apple Watch measures, RIFitTest app data*,* and the fall-efficacy scale, as outlined in Table 1. This combined data set will then be analyzed descriptively and using longitudinal methods, as appropriate.

Descriptive statistics will be used to measure the following key parameters of feasibility of recruitment, enrollment, participation, and retention [21]: number of patients screened, eligible, and recruited; time required to recruit; number of patients unable to provide consent; number of dropouts; and number of patients with refusal and retention at each follow-up. Frequencies, proportions, rates, means and medians, standard deviations, and other measures of variability will be used to report on these feasibility measures.

Descriptive statistics will also be used to assess the following parameters of acceptability: the fall diary completion rates, days the Apple Watch was worn, and any malfunctions of the Apple Watch or app. We will use the Apple Watch–obtained data to determine the association between gait and fitness measures (eg, step count, stairs climbed, and resting heart rate) and reported falls. To account for the longitudinal nature of this data and within-person correlation, we will use generalized estimating equations or generalized linear models [22].

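### The Abstract asks about continuous or periodic use with or without telephone help, but everyone is called and wear is summarised only as days worn

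*Protocol article*

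**What the plan says.** The Abstract (Methods) states that the field test will determine whether patients and caregivers can use the watch, phone and app "either (1) continuously or (2) periodically, with or without telephone assistance from the research staff". The body of the article then describes the following.

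- **Wear instruction (ED Procedures).** Training covers "when to use the Apple Watch (ie, continuously, including while bathing and participating in water activities". No periodic wear is taught. Table 1 nevertheless gives the timing of the sensor measures as "Baseline ± continuously (days 1 to 30", and the plus-or-minus sign is not explained.
- **Staff contact (Follow-up Procedures).** "All participants will be contacted by research staff on days 3, 8, 15, and 22", and the purpose is "to remind them to complete the steps in the study protocol and to answer questions". Table 1 describes these contacts as phone sessions and says their timing and length are recorded.
- **Participant-initiated help (Abstract, Methods).** Everyone also receives "a number to call if they have questions about the research protocol or device usage". Use of that number is not among the listed parameters.
- **Quantitative measures (Sensor and Survey Data Collection and Analysis).** The listed acceptability parameters are "the fall diary completion rates, days the Apple Watch was worn, and any malfunctions of the Apple Watch or app". The same section says the watch sensors supply continuous data.
- **Qualitative measures (Poststage Interview Content).** The closing interview covers how use changed over time, barriers to daily use, and the quality of telephone support.

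**The concern.** The stated question has two parts: how the devices are used, and whether they are used with or without telephone help. The Methods supply one instruction on wear and one level of telephone support. The planned measures do not recover either distinction from what participants actually do.

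This matters because the results are meant to improve the app and the training for a subsequent clinical trial. The article itself gives waning interest in wearables as a reason for field-testing first. The designers of that trial will want to know how much staff contact lay behind the adherence seen, and whether the watch was on for most of the day or only part of it. As planned, the report would give adherence under repeated reminders and a count of days, while the Abstract suggests it will say more.

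**Working it through.** **1. The plan's own figure.** Four age groups of 5, plus 5 cognitively impaired patients, plus 5 caregivers: 4 × 5 + 5 + 5 = 30, of whom 4 × 5 + 5 = 25 are patients. Both figures reproduce. The groups are defined by age, cognition and caregiver role; none is defined by wear mode or telephone support. The article states no alpha, power or effect size, so no power calculation applies.

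**2. Telephone half.** Inputs: calls on days 3, 8, 15 and 22 to all participants (Follow-up Procedures); active tasks on days 1, 7, 14, 21 and 28 (Table 1); 30 days of participation.

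- Participants uncalled by design: 0 of 30.
- Days before the first call: 3 − 1 = 2, so 2/30 = 6.7% of follow-up.

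| Task due on day | Calls already scheduled | Days since last call | Days to next call |
|---|---|---|---|
| 1 | 0 | none yet | 3 − 1 = 2 |
| 7 | 1 | 7 − 3 = 4 | 8 − 7 = 1 |
| 14 | 2 | 14 − 8 = 6 | 15 − 14 = 1 |
| 21 | 3 | 21 − 15 = 6 | 22 − 21 = 1 |
| 28 | 4 | 28 − 22 = 6 | no further call; closing interview on day 30 |

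Three things follow.

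- Only the day 1 session, right after training, precedes every call.
- The number of calls received rises in step with time in the study, so the two cannot be separated.
- The sessions on days 7, 14 and 21 are each followed by a call one day later. A late completion may therefore have been prompted by that call, and an overall completion rate would not show it.

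**3. Wear half.** The article does not define a day worn. *Assumption:* any wear counts. Illustrative wear times, held for all 30 days:

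| Hours per day (assumed) | Days worn | Share of the day (hours/24) |
|---|---|---|
| 1 | 30/30 | 4% |
| 4 | 30/30 | 17% |
| 8 | 30/30 | 33% |
| 12 | 30/30 | 50% |
| 22 | 30/30 | 92% |

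A stricter definition narrows the problem without removing it. If a day counted only from 8 hours up, the last three rows would still all score 30/30, with wear from 33% to 92% of the day. Under either rule, the count shows skipped days but not the pattern within a day.

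**The case against.** The strongest reply is that the Abstract promises no comparison. It asks whether people can use the devices in these ways, and elsewhere the objective is plainly feasibility, acceptability and usability. *Periodically* may simply mean the daily surveys and weekly tasks, which every participant does; the analysis section does separate continuous sensor data from episodic data. The interviews ask about patterns of use and telephone support, call timing and length are recorded, and the definition of a wear day may sit in a fuller document.

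Much of this stands. A reader might infer that the study needed four arms, or that its question cannot be answered at all. The article supports neither. It sets up no four-way contrast, skipped days will be visible, and the raw sensor stream may yield within-day wear.

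A reader might also infer that the reported completion rate will overstate unassisted ability by some known amount. The article has no data from which to estimate such a difference.

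What the reply does not meet is narrower. No reading of the Methods provides sustained use without staff calls. The article never says that *periodically* means the app tasks. Interviews give recall and opinion, not hours worn or the timing of completion. Call records show the support given, but everyone is given it.

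**Conclusion.** The point holds in a limited form, as a cheap improvement. By design, 0 of 30 participants are followed without scheduled calls, and 2 of 30 days precede the first one, so use without telephone assistance is not observed beyond that. The listed wear measure cannot tell continuous from part-day wear. That rests on a day count being reported without hours; how wide the blind range is depends on the undefined wear-day rule. No sample size or power figure is affected.

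It would be tempting to treat the day 28 session as the least-prompted one, because it falls six days after the last call. The schedule does not support that: days 14 and 21 also fall six days after the preceding call, and day 28 follows four calls, the most of any session. What is distinctive about day 28 is that it is the only weekly session after day 1 with no scheduled call the next day.

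**What to change.** (a) Alongside days worn, report hours worn per day derived from the continuous sensor data, with a pre-set cut-off that classes each person-day as continuous, part-day or no wear. This depends on recording density, which the article does not give and which should be checked first. The cut-off must allow for the mealtime charging that participants are taught.

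(b) For tasks due on days 7, 14 and 21, report completion before and after the calls on days 8, 15 and 22. Label the first category *before that session's follow-up call*, not *unprompted*, because earlier calls and app notifications will already have occurred. Use the completion time on the device, since some data may be entered manually during staff follow-up. Report day 28 separately, noting only that no call is scheduled for the next day.

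(c) Tabulate staff call time per person from the session records already planned, and add a simple log of help-line calls.

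(d) Restate the Abstract's claim as use under scheduled telephone support, say what continuous and periodic use mean, and reconcile the Table 1 timing with the wear training.

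Cost: some extra programming and one small new log. No new arms, participants or contacts are needed.

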**Results:**

Recruitment began in December 2019 and was on pause from April 2020 until September 2020 due to the COVID-19 pandemic. Study recruitment will continue until 30 participants are enrolled. This study has been approved by the Rhode Island Hospital Institutional Review Board (approval 1400781-16).

**Conclusions:**

GAPcare II will provide insights into the feasibility, acceptability, and usability of the Apple Watch, iPhone, and the RIFitTest app in the population most likely to benefit from the technology: older adults at high risk of recurrent falls. In the future, wearables could be used as part of fall prevention interventions to prevent injury before it occurs.

**Trial Registration:**

ClinicalTrials.gov NCT04304495; https://clinicaltrials.gov/ct2/show/NCT04304495

**International Registered Report Identifier (IRRID):**

DERR1-10.2196/24455

## Introduction

Falls are the leading cause of emergency department (ED) visits for injuries in older adults aged 65 and older [1,2]. Each year in the United States, 28.7% of older adults sustain a fall, resulting in 2.8 million annual ED visits for geriatric falls [3]. The risk of recurrent falls is particularly high immediately after the ED visit [4]; 31% of community-dwelling older adults in the United States fall again within 6 months, and 62% of these falls cause serious injury [5,6]. Technology-based interventions initiated immediately after the ED visit could be useful to prevent falls, if they are embraced by older adults.

Wearable technology, while conventionally targeted toward a younger population, has shown promise in older adults. One recent prospective study with 95 community-dwelling older adults found as many as 91% of participants rated a wearable watch as acceptable and easy to use [7]. Additionally, the Apple Heart Study, launched in 2017, recruited over 24,000 older adults to monitor their heart rhythm for atrial fibrillation using the Apple Watch and an iPhone app [8], indicating that this population can use these devices. Furthermore, a recent systematic review showed that exercise, compared to educational or environmental interventions, significantly reduced falls in older adults, although increased walking alone did not decrease falls [9]. Wrist-worn technologies may increase daily step counts [10] and encourage exercise tracking, which could facilitate fall prevention. Fitness tracking has the additional psychological benefit of allowing individuals to have control of their subjective well-being, how people experience and evaluate the quality of their lives [11].The prospect of these devices for fall-related measures in older adults remains a relatively untapped area for application of this technology.

The Apple Watch (Apple Inc) is a wearable device with built-in sensors that can detect falls automatically using its accelerometer and gyroscope sensors. Unlike traditional fall alert pendants, the Apple Watch alerts designated contacts and emergency medical services even if the individual is unconscious or immobile. The Apple Watch is particularly well-suited as a research tool because fall occurrences and other sensor data (eg, heart rate and step count) are recorded in HealthKit, a developer application programming interface included in the iPhone operating system (iOS) [12]. Additionally, Apple provides developers with open-source code for cognitive and motor tests called *active tasks*, which allow participants to perform assessments independently at home with the help of visual, tactile, and auditory prompts generated by the iPhone. Results of these assessments, as well as fall occurrences and other HealthKit-collected data, are recorded into our novel research app Rhode Island FitTest (RIFitTest) and transmitted to Research Electronic Data Capture (REDCap) [13] in real time for monitoring and analysis by the research team.

We used the Unified Theory of Acceptance and Use of Technology (UTAUT) model as a conceptual framework when developing our protocol. The UTAUT model, which is a combination of eight prominent theories—the Theory of Reasoned Action, Innovation Diffusion Theory, the Theory of Planned Behavior (TPB), the Technology Acceptance Model (TAM), the combined TAM-TPB, Social Cognitive Theory, the Motivational Model, and the Model of Personal Computer Utilization—has been extensively tested across multiple disciplines and has been validated as an effective tool to assess acceptance of health-related technology [14]. In the UTAUT model, four constructs play a significant role as determinants of user acceptance and usage of technology: (1) performance expectancy, (2) effort expectancy, (3) self-efficacy, and (4) facilitating conditions.

In this mixed methods study—the Geriatric Acute and Post-Acute Fall Prevention Intervention (GAPcare) II—we will conduct field-testing with older adult ED patients, with and without cognitive impairment, who present to the ED with a fall within the last 7 days, as well as with their caregivers, to assess the feasibility, acceptability, and usability of the Apple Watch, iPhone, and the RIFitTest app to assess gait, fitness, and/or subsequent falls.

## Methods

### Study Design

Because we are interested in reducing recurrent falls among older adult ED patients, we designed a mixed methods study to collect perspectives from older adults and their caregivers through semistructured interviews (ie, qualitative data) and information about falls and fall risk factors prospectively (ie, quantitative data). Fall risk factors include impairment in cognition, impairment in mobility, fear of falling, and heart rate abnormalities, all of which can be measured by wearable device sensors or through survey questions on mobile devices. This study was registered at ClinicalTrials.gov (NCT04304495).

### Field-Testing Nature of the Study

Older adults face unique challenges with using mobile devices, and many studies have shown that interest in using wearables often wanes after initial recruitment [15]. Therefore, we decided we needed to first field-test our protocol among older adults to ensure they would express interest in participating, be able to learn how to use the technology, and stay continuously engaged in the study. A field test is a type of testing that evaluates technology performance in real-world settings. This allows for an enhanced understanding of how the target end user experiences the product and can lead to design optimization and insights into challenges that must still be overcome.

### Planning Phase

During the planning phase, we assembled experts in digital health, qualitative research, geriatrics, neurocognitive assessments, and clinical research. This team advised the principal investigator (EG) on the protocol, outcome assessment, and implementation of the study. We also programmed our survey questions in REDCap, created the app, and tested the app among our research staff during this time.

### Information Technology Solution

To collect the sensor and survey data generated on the Apple Watch and to transfer the data to our secure server, we needed to develop an iOS app. We engaged one of the study authors (CM) to assist with creating the app for the study using his third-party platform, status/post [16]. Status/post integrates REDCap and ResearchKit and allows researchers to design the app in the same way questionnaires are designed in REDCap, reducing costs and turnaround time because a developer is not necessary.

### RIFitTest Study App

This app, when paired with the Apple Watch and the user’s iPhone, collects sensor-obtained data *passively*. Users can also enter data *actively* using their phones. Several steps are required to create the research app, RIFitTest:

Enter survey questions and answers into REDCap data collection software.Choose Apple HealthKit measures (eg, heart rate and steps) and enter Apple Inc open-source code into the field notes of REDCap to extract sensor data from the watch and store it in REDCap.Select Apple ResearchKit *active tasks* relevant to the study and enter Apple Inc open-source code into the field notes of REDCap.Use status/post to schedule notifications for participants, create participant usernames and passwords, and monitor participant activity.Post app on Apple App Store to allow participants to download the app onto their iPhones.

After creation of the app, we will pilot-test it among the research staff and make changes to improve the usability for older adults (eg, increase font size and choose the color of the app to enhance readability). Only participants who complete the consent process will be able to download the study app. When installing the RIFitTest app, participants will enter a username and password created by the study team and will permit the app to access each category of data stored in Apple HealthKit (eg, heart rate and step count).

### Data Security, Transmission, and Storage

Data from the device will be pushed to the Health Insurance Portability and Accountability Act (HIPAA)-compliant REDCap program when participants connect to a Wi-Fi network, or the data will be added to the REDCap program manually during follow-up with the research team. We will use an application programming interface to ensure data can be viewed in real time on the REDCap program. Data transmission is encrypted with Secure Sockets Layer. Similar to other iOS-based apps, the RIFitTest app is “sandboxed,” meaning that no other apps can gather data collected by the study app. The app is password protected, which prevents user data from being revealed if the device is stolen.

